## Abstract

**Introduction::**

Knee arthroplasty also known as the total knee replacement is an orthopedic surgical procedure done to resurface the knee that has been severely damaged by arthritis. After the completion of the surgical procedure, the skin closure is done. The optimal goal of skin closure after the procedure is to promote rapid healing and an acceptable cosmetic result while minimizing the risk of infection. Skin closure after knee arthroplasty is done by using either of the two widely used sutures i.e., polypropylene (Prolene) sutures or the skin staple sutures. There are no standard guidelines as which type of the suture should be used. The present study aims to compare the incidence of surgical site infections (superficial and deep) for Prolene vs staple sutures in the bilateral knee arthroplasty patients within 6 weeks for superficial and within 90 days for deep infection.

**Methods::**

This study will be conducted as an open blinded, parallel design, equivalence randomized controlled trial. The patients would be selected and randomized in 1:1 ratio to receive either of the two interventions i.e., Prolene or Staples. Patients undergoing unilateral or staged total knee replacement (TKR) were excluded.

**Analysis::**

The normality assessment will be done using Shapiro Wilk test. Cox proportional hazard regression will be used to check the univariate and multi-variable associations of independent variables with the outcome. Both intention to treat analysis and per protocol analysis would be performed.

**Ethics and Dissemination::**

All the required approvals will be taken from the ethical review committee. Informed consent will be taken form the patient to enroll him/her in the study. Results of the study will be disseminated to the study participants, public health and clinical professionals and would also be published in a reputable international journal.

The trial is registered at *clinicaltrials.gov* and UIN of the registry is NCT04492852.

**Highlights:**

## 1. Introduction

With the increasing advancements in the science of accelerated rehabilitation, more pressure has been placed on the shoulders of the surgeons to perform more surgeries in a day and to reduce the length of hospital stay of the patients [1]. Knee arthroplasty is an orthopedic surgical procedure done to resurface the knee that has been severely damaged by arthritis [2]. It is a procedure performed to relieve the pain and minimize the damage and disability done to the knee [3]. Osteoarthritis is the most common cause resulting in the need for knee arthroplasty [4]. Osteoarthritis is the most common form of arthritis that affects millions of individuals worldwide [5]. Osteoarthritis is a degenerative disease of the joints that affects the joint cartilage and the bones surrounding it. It can affect almost any joint in the body but most commonly if affects the joints of knees, hands, spine and hip [5]. It causes pain, stiffness, grating sensation, loss of flexibility and bone spurs.

The damage and disability done to the knee by osteoarthritis is treated by doing knee arthroplasty in which parts made up of metal or plastic are used to cover the ends of the bones forming the knee joint [5]. After the completion of the surgical procedure, the skin closure is done. The optimal goal of skin closure is to promote rapid healing and an acceptable cosmetic result while minimizing the risk of infection [6]. Skin closure after knee arthroplasty is done by using either of the two widely used sutures i.e. polypropylene (Prolene) sutures or the staple sutures [7]. Prolene sutures are made up of a synthetic steroisomer known as polypropylene. It is a monofilament non-absorbable, sterile surgical suture [8]. They are indicated for use in general soft tissue. It provides permanent tensile strength retention in tissue, even in the presence of infection [8]. These sutures are exceptionally smooth for an easy passage through the tissue. Prolene sutures are widely used in cardiovascular, orthopedics, ophthalmic, and neurological surgical procedures [8]. Another type of sutures that are used to close the surgical wound are the staple sutures. They are used as an alternative to the traditional Prolene sutures [1]. They are non-absorbable and usually used on surgical wounds that are big, complex, or hard to close by using Prolene. These are specialized staples made up of titanium, stainless steel or plastic [9].

### 1.1 Rationale

Post-operative surgical site infections and complications are a major concern nowadays. It not only increases the length of hospital stay of the patient but, it also increases the healthcare cost and burden on the healthcare system. Both these types of sutures are commonly used to close the wounds after surgery. Skin staples are not widely used as compared to Prolene because they are expensive and not easily available in every hospital. A study of hip arthroplasty patients has shown that the risk of developing an infection in wounds closed with staples is 4 times as compared to the wounds closed with Prolene sutures [10]. A meta-analysis concluded that the risk of a wound infection was three times greater in wounds closed with staples as compared to the Prolene [6]. The results have been inconclusive of the studies conducted on the patients of knee arthroplasty [1].

In a study of 181 patients comparing staples and prolene, they reported significantly difference in complication rate between the two groups; the staples group had no complications while the suture group had 9 (9.1%) complications [11]. In another systematic review and metanalysis, they reported that both methods of closure are equivalent and suggested to choose for the economical method, sutures [12]. Moreover, there are no standard guidelines as which type of the suture should be used. The type of sutures is being selected on the orders and wishes of the surgeon at the time of skin closure.

### 1.2 Objectives

#### 1.2.1 Primary objective

➢ The primary objective of the study is to compare the incidence of surgical site infections (superficial and deep) for Prolene vs staple sutures in the bilateral simultaneous knee arthroplasty patients within 6 weeks for superficial and within 90 days for deep infection.

#### 1.2.2 Secondary Objective

The secondary objective of the study is to compare the incidence of postoperative complications bleeding, Hematoma, Seroma, pain) within 2 weeks.To compare the pain scores at the time of removal of Prolene sutures and staples.

### 1.3 Hypothesis

#### 1.3.1 Null Hypothesis

There is a difference in the incidence of surgical site infection in bilateral simultaneous TKR patients with wound closure by Prolene vs staple.

#### 1.3.2 Alternative Hypothesis

There is no difference in the incidence of surgical site infection in bilateral simultaneous TKR patients with wound closure by Prolene vs staple.

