## 2. Methods

### 2.1 Study Design

This study will be conducted as an open blinded, parallel design, equivalence randomized controlled trial. The patients would be randomized to receive either of the two interventions i.e., Prolene or Staples.

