### 2.8 Sample Size

The sample size was calculated via open epi software version 3.01. The level of significance was kept at 5% with a power of 80%. The percentage of exposed (staple sutures) with outcome (surgical site infection) was 66%. The percentage of non-exposed (Prolene sutures) with outcome (surgical site infection) was 33%. The estimated risk ratio taken from a study was 2. After adding the non-response rate of 10% the final sample size came out to be 82 patients with 41 patients in each arm [3].

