### 3.2 Univariate and Multivariable Analysis

The Cox Proportional Hazard regression will be used for the univariate and multivariable analysis. Univariate analysis will be conducted, and crude risk ratios and their 95% confidence intervals will be obtained. All significant independent variables at the univariate stage will be regressed by using cox proportional hazard regression using the stepwise method in the multivariable model and the adjusted risk ratios will be obtained. Both per-protocol analysis and intention to treat analysis (ITT) would be performed.

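### The trial is declared an equivalence trial, but no equivalence margin appears in its hypotheses, sample size or analysis, so equivalence cannot be established as planned

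*Protocol article*

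**What the plan says.** Section 2.1 calls the study an "open blinded, parallel design, equivalence randomized controlled trial", and the Abstract repeats the label. Section 1.3.1 gives the null as "There is a difference in the incidence of surgical site infection in bilateral simultaneous TKR patients with wound closure by Prolene vs staple". Section 1.3.2 gives the alternative as "There is no difference in the incidence of surgical site infection in bilateral simultaneous TKR patients with wound closure by Prolene vs staple". The usual roles of the two hypotheses have been reversed, as an equivalence design requires, but neither statement contains a margin, and none appears elsewhere in the article.

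Section 2.8 sizes the trial on infection in 66% of the staple arm and 33% of the Prolene arm, at 5% significance and 80% power. It adds that "The estimated risk ratio taken from a study was 2" and, after 10% for non-response, arrives at 82 patients, 41 per arm. Section 2.10.1 anticipates an infection rate of 2%–7%.

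Section 3.2 plans Cox regression, from which "crude risk ratios and their 95% confidence intervals will be obtained", followed by a stepwise multivariable model. Both intention-to-treat (ITT) and per-protocol analyses are planned. No threshold is attached to the interval, and no rule for concluding equivalence is stated.

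**The concern.** In an equivalence trial the margin defines the question. It turns the null into a difference at least as large as the margin and the alternative into a difference smaller than it, and it drives both the sample size and the decision rule. Without it, the null in 1.3.1 covers every non-zero difference, however small. A confidence interval of non-zero width can never exclude all of those, so the alternative in 1.3.2 cannot be demonstrated with any amount of data.

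The other components belong to a trial that looks for a difference: two unequal planning rates in 2.8, and in 3.2 a regression whose standard test has no difference as its null, the opposite of 1.3.1. With no criterion for equivalence, the conclusion that lies nearest to hand is that a non-significant result means the closures are equivalent. That inference has no controlled error rate. Section 5 says the findings will go to the surgeons of the service line in order to standardise practice, so an unsupported equivalence claim could have direct consequences.

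**Working it through.** **1. Reproduce the 82.** Inputs from 2.8: p1 = 0.66, p2 = 0.33, significance 5%, power 80%, 10% non-response. Two-sided testing is assumed, because the section does not state sidedness. Kelsey formula with p̄ = (0.66 + 0.33)/2 = 0.495:

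n = (1.960 + 0.842)² × 2 × 0.495 × 0.505 / 0.33² = 36.03, so 37 per arm.

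37 × 1.10 = 40.7, so 41 per arm and 82 in total. This matches the stated figure exactly. One-sided versions give totals of 62 to 76 and do not match. The number is therefore fully explained as a size for detecting a difference, and no equivalence margin entered it.

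**2. What a non-significant result would mean.** At 2%–7%, the expected number of infections among 82 patients is 82 × 0.02 = 1.6 to 82 × 0.07 = 5.7. Exact binomial enumeration with 41 per arm, two-sided 5% tests:

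| True rates | Non-significant, chi-square | Non-significant, Fisher |
|---|---|---|
| 7% vs 3.5% (risk ratio 2, as in 2.8) | 90% | 98% |
| 7% vs 2% (ends of the 2.10.1 range) | 83% | 97% |

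These are probabilities of missing a difference. They use simple tests of proportions in place of the planned Cox model.

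**3. The tightest interval 82 patients can give.** With no infections in either arm, the Newcombe limits for the risk difference reduce to ± z²/(n + z²):

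- 90% interval, n = 41: 2.706/43.706 = ±6.2 points
- 90% interval, n = 37: 2.706/39.706 = ±6.8 points
- 95% interval, n = 41: 3.842/44.842 = ±8.6 points

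A check of every possible table at 41 per arm finds none whose 90% limits both lie closer to zero than 6.2 points.

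**4. Power for equivalence.** The article gives no margin, so the margins here are assumptions that show the range. If the true rates are equal and there are 41 per arm, the exact probability that the 90% Newcombe interval lies inside the margin is:

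| Margin | Common rate 2% | Common rate 7% |
|---|---|---|
| ±5 points | 0 | 0 |
| ±10 points | 35% | 8% |

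For two one-sided 5% tests with 80% power and a true difference of zero, n = 2p(1 − p)(1.645 + 1.282)²/margin². A 5-point margin needs 135 evaluable patients per arm at 2%, 295 at 4.5% and 447 at 7%. This normal approximation is optimistic with so few events: for ±10 points at 2% and 41 per arm it gives 89%, where the exact Newcombe figure is 35%.

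**The case against.** The strongest reply concerns the decision rule. A reader might infer that the protocol intends to treat p > 0.05 as equivalence, or that this is the only route it leaves. It does not say so. Section 3.2 gives no decision rule, its significance screening selects variables for the multivariable model, and the 95% interval it plans is the standard tool for an equivalence decision once there is a margin. ITT and per-protocol analyses also suit such a design. A detailed rule could sit in an analysis plan that is not shown. All of this stands, and reliance on non-significance is therefore the natural inference, not a stated plan. It does not excuse the missing margin, because the article prints its hypotheses and sample-size inputs and the 82 is explained exactly without one.

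A reader might also infer from the 90%–98% figures that equivalence would be wrongly concluded nine times in ten. That does not follow. A true 7% against 3.5% is a difference of 3.5 points, which lies inside any risk-difference margin attainable at this size. Calling the arms equivalent would be an error only under a margin of 3.5 points or less, or under a ratio margin that excludes 2. The figures show low power to detect a difference and are not a false-equivalence rate.

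Finally, the low event count comes from the gap between the 66%/33% planning rates and the anticipated 2%–7%. That is a separate defect, and the missing margin would remain even if the planning rates were right.

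**Conclusion.** The point holds and should be corrected before the trial draws any equivalence conclusion. The declared design, the hypotheses and the sample size contradict one another: the first requires a margin, and the other two are stated in full without one. The alternative of exact equality cannot be established, and an equivalence conclusion would have no controlled error rate.

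The firmest measure of size is the floor on precision: ±6.2 points with 41 evaluable per arm, about ±6.8 with 37, against an anticipated rate that is itself only 2%–7%. This rests on the 90% Newcombe interval for the risk difference; other methods or a ratio scale would give different figures. The conclusion about the missing margin rests on none of these calculations.

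**What to change.** - **Section 1.3:** restate the null as a difference at least as large as a margin and the alternative as a difference smaller than it. Justify the margin and fix it in advance. Either the risk difference or the risk ratio may be used; the ratio is the measure already named in 2.8 and 3.2.
- **Section 3.2:** declare equivalence only if the confidence interval lies wholly within the margin in both the ITT and per-protocol sets, and otherwise report the result as inconclusive. A 90% interval corresponds to two one-sided 5% tests; the planned 95% interval is stricter and also valid. State that a non-significant p-value is not evidence of equivalence.
- **Section 2.8:** say that 82 was derived for detecting a difference, and restate the power for equivalence at the chosen margin and at realistic infection rates.
- **If no clinically acceptable margin is attainable with 82 patients:** remove equivalence from the Abstract, 1.3, 2.1 and the conclusions, and report the difference with its confidence interval.

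The cost is a revision of wording in these sections and one recalculation. The downside is that the trial may have to report an inconclusive result or give up the equivalence claim.

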## 2. Methods

### 2.1 Study Design

This study will be conducted as an open blinded, parallel design, equivalence randomized controlled trial. The patients would be randomized to receive either of the two interventions i.e., Prolene or Staples.

### 2.2 Study Site

The study would be conducted at the Aga Khan University Hospital, Karachi. The AKUH has a well-established medical records system and clinical trial unit (CTU) to facilitate clinical trials. Both the interventions being used in this study i.e. The patient would be recruited pre-operatively in the consulting clinic when the patient will book an appointment for the surgical procedure of bilateral simultaneous TKR. The intervention will be performed on the patient in the operating room while the knee arthroplasty surgery is being performed. Only one surgeon (surgeon A) will perform the intervention on the patient that will be selected prior to starting the study, to minimize the variability in incision techniques and post-operative management.

### 2.3 Study Interventions

The study will have 2 intervention arms. The patients will be randomized to receive either Prolene sutures for wound closure or staple sutures for wound closure. After the application of the intervention, the routine care would be given to the patients postoperatively.

### 2.4 Randomization

The patients would be randomized in 1:1 allocation to either receive Prolene sutures or the staple suture. Randomization will be done by the clinical trials unit (CTU) of AKUH using the specialized computer software. The computer-generated random allocation will ensure that nobody including the investigator, or the study team are able to influence it. Simple randomization process will be carried out using a block technique to assign the allocation. After completing the process of randomization, the details identifying the patient and the envelope number would be recorded on a form and will be returned to the trial administration to confirm the recruitment of the patient into the study.

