### 2.5 Blinding

This study would be an open label trial. Due to the different nature of the visible marks of the sutures, it would not be possible to blind the study team, the PI, the surgeon, and the outcome assessor (SSI nurse) from the intervention administered. The surgical site infection nurse who assesses the surgical wounds post-operatively in the hospital as well as in clinics during follow up visits would be blinded to the hypothesis of the study. The other outcome assessors such as the pathologist who will conduct tests on the specimen taken from the surgical site, to confirm the presence of an infection would be blinded to the intervention.

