### 2.9 Recruitment

For this study, the non-probability consecutive sampling technique will be used. All the patients opting for surgeon A to undergo elective bilateral simultaneous TKR during the specified period for recruitment will be included in the study. By using the consecutive sampling technique, the probability to miss out on participants would be relatively small. Firstly, the patients opting to undergo bilateral simultaneous TKR under care of the selected surgeon would be identified and would be assessed against the eligibility criteria of the study. Secondly, the eligible patients would be briefed about the study and the interventions of the study. Furthermore, an informed consent would be obtained from the patient. The duration of the trial would be 2 years. During the first year of the study, the participants would be recruited until the desired sample size is achieved. After the surgical procedure, the patients will be followed for a year to assess the incidence of the surgical site infection.

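### Section 2.4 ties the patient to an envelope number and confirms recruitment only after randomisation; in an open-label, single-surgeon trial, registration should come before the allocation is revealed

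*Protocol article*

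**What the plan says.** All of this is in the protocol article.

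- **Allocation (2.4 Randomization).** "Randomization will be done by the clinical trials unit (CTU) of AKUH using the specialized computer software", in a 1:1 ratio. The safeguard given is: "The computer-generated random allocation will ensure that nobody including the investigator, or the study team are able to influence it".
- **Registration (2.4).** "After completing the process of randomization, the details identifying the patient and the envelope number would be recorded on a form". The form then "will be returned to the trial administration to confirm the recruitment of the patient into the study".
- **Before randomisation (2.2 Study Site, 2.9 Recruitment).** Patients are recruited in the pre-operative clinic, checked against the eligibility criteria and briefed. "Furthermore, an informed consent would be obtained from the patient". No entry with the CTU before allocation is described.
- **Masking and surgeon (2.5 Blinding, 2.2).** "This study would be an open label trial". A single preselected surgeon carries out every procedure.
- **Analysis sets (3.2).** "Both per-protocol analysis and intention to treat analysis (ITT) would be performed". Neither set is defined in the article.

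**The concern.** Intention to treat protects the comparison only if everyone randomised is counted. The safest way to ensure this is to have each patient on a central list before anyone can know the arm. Section 2.4 puts the steps the other way round: randomise, then record who the patient was and which envelope was used, then tell trial administration.

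The assurance that nobody can influence the allocation concerns how the sequence is generated. It does not cover who is registered afterwards. The weak point would therefore remain with an unpredictable sequence and sealed envelopes, and it is separate from any question about simple versus blocked randomisation.

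The setting gives it some weight. The team and the surgeon know the closure method, and section 1.1 reports that closure is at present decided by surgeon preference. If a patient allocated to the less favoured closure were not registered, and such patients differed in infection risk, one arm would lose them selectively. In an equivalence trial, that could create a difference or hide one.

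**Working it through.** **Step 1: order of events.** Setting sections 2.2, 2.9 and 2.4 side by side gives: identify and screen; brief; consent; randomise; write identity and envelope number on a form; return the form; recruitment confirmed. The first record described as linking a named patient to an envelope comes after randomisation. The article does not say who completes the form, when the envelope is opened relative to it, or how soon it is returned.

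**Step 2: patients per arm.** Section 2.8 gives 82 in total, 41 per arm, from 66% versus 33%, 5% significance, 80% power and 10% non-response. The Kelsey formula with two-sided 5% reproduces it:

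- mean proportion = (0.66 + 0.33)/2 = 0.495; difference = 0.33
- n per arm = 2(1.96 + 0.8416)² × 0.495 × 0.505 / 0.33² = 36.03, rounded up to 37
- total 74; 74 × 1.10 = 81.4, rounded up to 82

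**Step 3: expected infections.** Section 2.10.1 anticipates a rate of 2% to 7%.

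- 41 × 0.02 = 0.82 per arm
- 41 × 0.07 = 2.87 per arm

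**Step 4: effect of leaving out one infected patient.** With k infections among 41, the arm moves from k/41 to (k − 1)/40, a fall of (41 − k)/1640.

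| k | Before | After | Fall (points) |
|---|---|---|---|
| 1 | 1/41 = 2.4% | 0/40 = 0% | 2.4 |
| 2 | 2/41 = 4.9% | 1/40 = 2.5% | 2.4 |
| 3 | 3/41 = 7.3% | 2/40 = 5.0% | 2.3 |

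With 3 infections in each arm, one omission moves the risk difference from 0 to −2.3 points. Two omissions (1/39 = 2.6% against 7.3%) move it to −4.8. At the sample-size rates (27/41 versus 14/41), one omission from the higher arm changes the difference only from 31.7 to 30.9 points. The sensitivity comes from the low event rate.

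**Step 5: an illustration on assumed inputs.** Suppose the two closures are equal, a quarter of patients carry a 15% risk and the rest 2.5%. The overall risk is 0.25 × 0.15 + 0.75 × 0.025 = 5.63%. If a fraction f of one arm's high-risk patients goes unregistered, that arm's expected incidence is [0.25(1 − f) × 0.15 + 0.75 × 0.025] / [1 − 0.25f].

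| f | Patients lost (41 × 0.25 × f) | Incidence | Risk ratio |
|---|---|---|---|
| 1/4 | 2.6 | 5.0% | 0.89 |
| 1/2 | 5.1 | 4.3% | 0.76 |
| 1 | 10.3 | 2.5% | 0.44 |

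With half lost, assumed risks of 10% and 1% give 0.70, and 15% and 4% give 0.83. None of these risks or losses comes from the documents.

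**The case against.** A reader might infer that the intention-to-treat denominator is fixed by the returned forms, and that patients can vanish from it without trace. The documents do not support either reading.

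- **The analysis set.** Section 3.2 names intention to treat without tying it to the form. The term ordinarily means everyone randomised, and the definition may stand in a full protocol or analysis plan that is not shown.
- **The form.** Section 2.4 names no one as completing it and does not say that they know the arm at that moment. Nothing describes or permits using an opened envelope for another patient.
- **Traceability.** Consent is taken beforehand (2.9), a case report form is kept for each participant (2.11), envelopes are numbered and the CTU generates the allocation (2.4). A consented patient without a form, or a gap in the envelope numbers, could be found. Five or ten patients missing from one arm would leave about 36 or 31 against 41, which is plain to see.
- **Ordinary behaviour.** A surgeon who dislikes the allocated closure may simply use the other one. Intention to treat keeps that patient in the allocated arm.
- **Level of detail.** Envelope reconciliation and the definition of analysis sets are commonly left out of an article, so their absence alone is no fault.

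All of this stands, and it limits the point to the order of steps. That order is stated rather than omitted, and it is the less protective one. Traceability helps only if someone checks.

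**Conclusion.** The point holds in a limited form. Section 2.4 confirms recruitment and links patient to envelope after randomisation, with no earlier registration described, in a trial where the arm is visible and one surgeon operates. This leaves room for a randomised patient to go unregistered once the arm is known. It does not show that this will happen, that such a patient would be excluded from the intention-to-treat set, or that the loss would go unnoticed.

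The size that can be supported is about 2.4 percentage points in an arm's incidence for each omitted infected patient. It assumes 41 per arm and the article's 2% to 7% rate. The risk ratios of 0.44 to 0.89 are arithmetically correct but rest on assumed risks and one-sided losses, so they only illustrate the mechanism. The change is a cheap improvement to a stated step and does not correct an error in the analysis.

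**What to change.** Reverse the order in section 2.4:

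1. After consent and the eligibility check, log the patient's identity with the CTU against the next envelope number, before the allocation is revealed.
2. State that this entry is the recruitment.
3. Keep the form completed after randomisation as confirmation only, and check it against the log.

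Add a sentence to section 3.2 saying that every logged patient is in the intention-to-treat set, in the allocated arm, whether or not the form comes back.

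The cost is one short extra step per patient, 82 in all, through the unit that already randomises, plus a sentence or two in each section. Some losses that might have gone unrecorded will become visible and will have to be reported. Sample size and treatment are unchanged.
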